## Abstract

*Background*. Depression is frequently accompanied by sleep disturbances including insomnia. Insomnia may persist even after mood symptoms have been adequately treated. Acupuncture is considered to be beneficial to adjust the state of body and mind and restore the normal sleep-awake cycle. This trial is aimed at evaluating the efficacy and safety of electroacupuncture on treating insomnia in patients with depression.* Methods*. We describe a protocol for a randomized, single-blinded, sham controlled trial. Ninety eligible patients will be randomly assigned to one of 3 treatment groups: treatment group (acupuncture), control A group (superficial acupuncture at sham points), and control B group (sham acupuncture). All treatment will be given 3 times per week for 8 weeks. The primary outcome is the Pittsburgh Sleep Quality Index (PSQI). The secondary outcomes are sleep parameters recorded in the Actigraphy, Hamilton Rating Scale for Depression (HAMD), and Self-Rating Depression Scale (SDS). All adverse effects will be accessed by the Treatment Emergent Symptom Scale (TESS). Outcomes will be evaluated at baseline, 4 weeks after treatment, 8 weeks after treatment, and 4 weeks of follow-up.* Ethics*. This trial has been approved by the Ethics Committee of Shanghai Municipal Hospital of Traditional Chinese Medicine (2015SHL-KY-21) and is registered with ChiCTR-IIR-16008058.

## 1. Background

Depressive disorders are among the most common psychiatric disorders in adults. Previous study identified major depressive disorder (MDD) as the second leading cause of disability worldwide and results in an enormous public health burden [1]. The estimation of lifetime prevalence of MDD in China is 3.3% [2], causing an urgent need to improve health services for these patients.

Except depressive disorders including negative emotions, anxiety, agitation, low self-esteem, and suicidal tendencies [3], MDD is frequently accompanied by sleep disturbances such as insomnia or hypersomnia [4]. Insomnia can be found in 80–90% of patients with MDD [5], characterized by persistent dissatisfaction with sleep quantity or quality, with specific complaints of difficulty falling asleep, frequent nighttime awakenings, and/or awakening earlier in the morning than desired [6]. For many patients, insomnia persists even after mood symptoms have been adequately treated.

At present, the treatment of comorbid MDD and insomnia is given priority to pharmacological treatment, complemented with cognitive behavioral therapy (CBT), sleep hygiene education, and other treatments [7–9]. Although the development of various classes of antidepressants and sedative-hypnotics, represented by selective serotonin reuptake inhibitors (SSRIs) and barbiturates, has considerably improved the efficacy and prognosis in the treatment, the currently available pharmacotherapy is unsatisfactory [10]. Long-term use of these medications can cause side effects such as excessive sedation, tolerance, addiction, neurological toxicity, or other psychiatric disorders [11, 12].

Acupuncture, as a widely recognized alternative therapy in clinical practice, has been used to treat depressive disorders and related sleep disturbances recently. According to the theory of traditional Chinese medicine, acupuncture provides overall coordination, helping to achieve the state of relative equilibrium of body and mind and to restore the normal sleep-awake cycle. Researchers believe that electroacupuncture (EA) treatment can promote the sleep quality by direct manipulation of autonomic nervous system (ANS) [13]. In addition, some trials have investigated that EA can improve depressive disorders caused by cancer [14] or poststroke [15] and can act on depression by protecting nerve cells in the hippocampus [16]. Although the number of studies on depression or insomnia by acupuncture increases every year, there is little focus on the effects of EA on comorbid depression and insomnia and the quality of these related RCTs remains stagnant due to the methodological limitations that reduce the credibility of the results [17].

To study the clinical effects of electroacupuncture on treating insomnia and alleviating depression and to resolve some logic problems of present acupuncture researches, we design this randomized, parallel-group, and single-blinded clinical trial with a sufficient follow-up period. As a preliminary experiment, we aim at observing the effects of EA treatment on sleep status by subjective and objective assessments and eliminating the placebo effect of EA by setting reasonable sham acupuncture method as well. The results will be helpful to demonstrate if EA is an effective and safe therapy for improving sleep quality and mental health for patients with depression. The findings will be shared with the healthcare professionals, general public, and relevant organizations through publication of manuscripts and conference presentations.

## 2. Methods/Design

### 2.1. Setting and Design

We will conduct a single-center, patient-assessor-blinded, randomized controlled trial to evaluate the efficacy and safety of electroacupuncture for insomnia in patients with depression. The trial will be performed at the acupuncture department in Shanghai Municipal Hospital of Traditional Chinese Medicine in Shanghai, China. We will recruit 90 patients who meet inclusion criteria and randomly assign them to one of 3 groups, receiving electroacupuncture, superficial acupuncture at sham acupoints, or sham acupuncture. After one week of washout period, patients will accept 12 weeks of observation (Table 1). All treatment will be given 3 times a week (every other day) for 8 weeks. Participants will be assessed at 4 time points, the baseline (1 week before treatment), the middle of the treatment (4 weeks after treatment starts), end of the treatment (8 weeks after treatment starts), and follow-up (4 weeks after treatment finishes). All participants will complete the assessments by the PSQI, Actigraphy, HAMD, SDS, and TESS. We will follow the Standards for Reporting Interventions in Clinical Trials of Acupuncture (STRICTA) [18] throughout the trial.

Figure 1 is a flowchart of the study.

#### 2.1.1. Inclusion Criteria

Participants meeting the following criteria will be included:Male or female participants aged 18–70Participants who meet the diagnostic criteria of depression according to the Diagnostic and Statistical Manual of Mental Disorders, Fourth Edition (DSM-IV) [19]Participants whose HAMD score is 20–35Participants who have complaint about insomnia at the first visit to the doctorParticipants whose PSQI score is more than 7Participants who voluntarily agree with the investigation and sign a written informed consent form for the clinical trial

#### 2.1.2. Exclusion Criteria

Participants who report any of the following conditions will be excluded:Participants with secondary depressive disorders caused by organic diseases, medicine, or psychotic disorders including schizophreniaParticipants who are in the depressive episode of bipolar disorder or suffering from dysthymia, reactive depression, and depressive syndrome caused by other diseasesParticipants with alcohol abuse or drug dependenceParticipants who refuse to wear the Actigraphy during the trialPregnant or lactating women

### 2.2. Sample Size Calculation

As a preliminary trial, the calculation of sample size is based on the open study about acupuncture for aging patients with depression and sleep disorders [20]. Referring to the study, the designer recruited 24 patients in each group to take acupuncture or sham treatment and also used PSQI as the main assessment indicator and suggested further study in controlled trials on the effects of acupuncture for younger patients with depression or insomnia. To study about the efficacy of electroacupuncture on depressive patients with insomnia, we positively take the previous results and 20% dropout rate into consideration and determine that the sample size of each group is 30 participants. With 1 : 1 : 1 allocation to each group, a total of 90 participants should be recruited.

### 2.3. Recruitment

The participants will be recruited through hospital-based advertisements from outpatient clinic and from website of Shanghai Municipal Hospital of TCM. If they have interest in participating, they can take the phone screening first and will be asked for screening visit in the hospital where they are asked to fill in some scales and then wear a wrist Actigraphy to monitor their sleep quality. The Actigraphy will be given to the participants for one evening and returned the next day. The data analyst will collect data from the Actigraphy and evaluate their sleep quality. Once the participants meet the inclusion criteria, they will be asked to sign the written informed consent form before intervention begins.

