### 2.9. Ethics

The trial has been approved by the Ethics Committee of Shanghai Municipal Hospital of Traditional Chinese Medicine, Shanghai, China (2015SHL-KY-21) and is registered with Chinese Clinical Trials Registry (ChiCTR-IIR-16008058). All patients will sign the written informed consent before participating in the trial.

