## Figures and Tables

**Figure 1 fig1:**
[figure not shown]
Flowchart of the trial. PSQI: Pittsburgh Sleep Quality Index; HAMD: Hamilton Rating Scale for Depression; HAMA: Hamilton Rating Scale for Anxiety; SDS: Self-Rating Depression Scale; TESS: Treatment Emergent Symptom Scale.

**Table 1 tab1:** Trial process chart.

	Baseline	Treatment phase			Follow-up phase
	Week 1	Week 0	Week 4	Week 8	Week 4
*Patients*					
Enrollment	×				
Signed informed consent		×			
Medical history	×				
Merger disease	×				
Randomization		×			
Intervention			×	×	
*Primary outcomes*					
PSQI	×		×	×	×
*Secondary outcomes*					
Actigraphy	×		×	×	×
HAMD	×		×	×	×
SDS	×		×	×	×
TESS			×	×	×
SSRIs dose record	×		×	×	×
Patients' compliance			×	×	×

**Table 2 tab2:** Acupuncture method for each acupoint.

Number	Acupoint	Needling method	Needles
1	Baihui (GV20)	The angle between the needle tip and the scalp is 30 degrees. Move the needle tip backward along the anterior-posterior midline, and then insert the needle for 0.5 cun.	0.3 *∗* 40 mm
2	Shenting (GV24)	The angle between the needle tip and the scalp is 30 degrees. Move the needle tip backward along the anterior-posterior midline, and then insert the needle for 0.5 cun.	0.3 *∗* 25 mm
3	Yintang (GV29)	Pinch the local skin, and then puncture obliquely for 0.5 cun	0.3 *∗* 25 mm
4	Anmian (EX-HN22)	The angle between the needle tip and the scalp is 30 degrees. Puncture perpendicularly for 0.5 cun with the needle tip to the nose tip.	0.3 *∗* 40 mm
5	Shenmen (HT7)	Puncture perpendicularly for 0.5 cun.	0.3 *∗* 25 mm
6	Sanyinjiao (SP6)	Puncture perpendicularly for 1 cun.	0.3 *∗* 40 mm
7	Neiguan (PC6)	Puncture perpendicularly for 0.5 cun.	0.3 *∗* 40 mm

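### Section 2.3 and Table 1 place signed written consent after the screening and baseline procedures, which conflicts with the consent statement in section 2.9

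*Protocol article*

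**What the plan says.** Four places in the protocol article bear on when written consent is obtained.

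- **Section 2.3 (Recruitment).** After a phone screening, candidates come to the hospital, where "they are asked to fill in some scales and then wear a wrist Actigraphy to monitor their sleep quality". The device goes home with them: "The Actigraphy will be given to the participants for one evening and returned the next day". A data analyst then evaluates the recording. Consent follows: "Once the participants meet the inclusion criteria, they will be asked to sign the written informed consent form before intervention begins".
- **Table 1 (trial process chart).** The row "Signed informed consent" has a single mark, in the Week 0 column, which is also where randomization is marked. Enrollment, medical history, PSQI, actigraphy, HAMD, SDS and the SSRI dose record are marked in the preceding baseline column.
- **Section 2.9 (Ethics).** "All patients will sign the written informed consent before participating in the trial".
- **Section 2.1.1 (Inclusion criteria).** Signing the consent form is the last criterion in the list, alongside a HAMD score of 20–35 and a PSQI score above 7.

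Section 2.1 adds that baseline is one week before treatment, and mentions a washout: "After one week of washout period, patients will accept 12 weeks of observation".

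**The concern.** A reader of section 2.9 would expect the form to be signed before anything is done for the purposes of the trial. The recruitment text and the schedule tie consent to the start of the intervention instead, so study procedures come first.

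Two things are at stake. The first is participant protection: the candidates have moderate to high depression scores, and they complete trial scales and overnight monitoring before signing. The second is the standing of the data. PSQI is the primary outcome, and HAMD, SDS and actigraphy are secondary outcomes, so the baseline values of every efficacy measure are scheduled before the signature.

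**Working it through.** No sample size, power or error-rate figure is involved. The check is of the order of events.

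**Step 1: order in the text.** Section 2.3 gives phone screening, then hospital visit with scales, then overnight actigraphy, then evaluation of the recording, then eligibility met, then consent, then intervention.

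**Step 2: order in the schedule.** From Table 1:

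| Row | Baseline (one week before treatment) | Week 0 |
|---|---|---|
| Enrollment | × | |
| Medical history | × | |
| PSQI, actigraphy, HAMD, SDS | × | |
| SSRI dose record | × | |
| Consent signed | | × |
| Randomization | | × |

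The gap between the baseline column and the consent mark is one week (baseline at one week before treatment, consent at Week 0). The result does not hang on how the table was typeset: the prose of section 2.3 also puts trial procedures before consent.

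**Step 3: can eligibility be settled without these measures?** No. Section 2.1.1 requires a HAMD range and a PSQI threshold. If consent is sought only after the criteria are met, both scales must already have been scored.

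**Step 4: are the procedures ordinary care?** That is not a natural reading. Section 2.3 concerns people answering trial advertisements, the recording is read by the trial's data analyst, and section 2.1.2 excludes anyone who refuses the device.

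**Step 5: comparison with sections 2.9 and 2.1.1.** Section 2.9 puts consent ahead of participation. Table 1 puts enrollment one column ahead of consent. On the natural meaning of the words these do not agree. Section 2.1.1 counts the signature among the criteria, while section 2.3 asks for it once the criteria are met; read literally, that is circular.

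**Step 6: where the washout falls.** Treatment lasts 8 weeks and follow-up 4 weeks, and 8 + 4 = 12, which accounts for the whole observation period. The one-week washout therefore comes before Week 0 and, if it starts at the baseline visit, fills the week before the consent mark. This is inferred: Table 1 has no washout row, and no section says where the washout stands relative to consent or what it consists of.

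**The case against.** The strongest reply is that participation in section 2.9 means being randomized and treated. On that reading it fits section 2.3, which requires the form before the intervention, and Table 1, where consent and randomization share Week 0. Enrollment is not defined and might mean no more than registration for screening. The reading is possible, but it is strained: it treats the baseline assessment of the primary outcome as lying outside the trial.

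The circularity can likewise be read away by taking section 2.3 to mean the other inclusion criteria. That is fair; it is a wording fault and adds little of its own.

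Three stronger conclusions that a reader might infer are not supported:

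- **That patients undergo the washout before consenting.** Taken alone, section 2.3 would allow the form to be signed the day after the screening actigraphy, hence before or during the washout. The washout's content is not described, and section 2.5 allows regular SSRIs to continue.
- **That the baseline data are gathered without permission.** The documents show only when the written form is signed. Candidates come forward voluntarily. No verbal or separate screening consent is described, but none is ruled out, and a condensed article may omit one.
- **That the analysis is compromised.** Section 2.8 analyses participants with at least one treatment. Someone who declines at Week 0 is never treated and so is not in that population, while everyone treated under the schedule will have signed. A claim that an audit would reject the baseline data goes beyond anything in the documents.

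Ethics approval is recorded in section 2.9, but the article does not show which consent sequence the committee saw, so approval does not settle the matter.

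**Conclusion.** The point holds in this form: section 2.3 and Table 1 both put signed written consent after screening and baseline procedures carried out for the trial, and this conflicts with section 2.9 on its natural reading. As scheduled, it affects all 90 planned participants, all four baseline efficacy measures, and the screening data of an unstated number of people who prove ineligible. By Table 1, consent comes about one week after the baseline assessments.

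The conclusion assumes that no separate screening consent exists; if one does, the remedy is to describe it and show it in the schedule. The placement of the washout before consent is an inference and is not needed for the finding. No power figure, effect estimate or planned comparison changes. What matters is the protection of participants and the standing of the baseline data, and the correction is simple enough that it should be made.

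**What to change.** - In Table 1, move the consent mark to the start of the screening or baseline visit, ahead of every other entry in that column.
- Reword section 2.3 so that written consent is signed at the screening visit before any trial scale, actigraphy or washout, with eligibility assessed afterwards and confirmed before randomization.
- Align sections 2.1.1 and 2.9 with that order, so that the signature is no longer both a criterion and something sought after the criteria are met.
- State where the washout falls relative to consent.
- Notify the ethics committee of the change.

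The cost is one table cell, a few sentences and the notification. The one drawback is that consent will also be taken from people who turn out to be ineligible. The planned sample size and analysis are unaffected.

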### 2.4. Randomization and Blinding

We plan to use the simple randomization method in this trial. An independent researcher will use the software SPSS20.0 to generate a random number table with the ratio of 1 : 1 : 1 to divide 90 participants into three groups. Then the researcher will make random allocation cards and seal each card in an opaque envelope whose number is the same as the time sequence in which eligible patients register for the trial. Another researcher will arrange the patients into different groups and tell the acupuncturists about the group assignment.

We will conduct a patient-assessor-blinded trial where participants are not aware of their group assignments and acupuncturists will not be involved in the outcome assessments or data analyses. We will make efforts to validate the successful implementation of the blinding method. Since the participants who have had previous acupuncture can more easily differentiate between real and sham treatment compared to inexperienced individuals [21], our recruiter will ask whether the patients have been treated by acupuncture for depression related insomnia before. Furthermore, participants will be asked to wear an eye mask before and during the treatment. Each treatment will be conducted in a closed unit with drape. Except the acupuncturists, other researchers including the statisticians, outcome assessors, and data analysts are all blinded to the group assignments. All researchers will accept training about the specification of this research method before the trial and strictly adhere to the task separation principle.

### 2.5. Intervention

Participants in three groups will receive different acupuncture or sham acupuncture methods. Participants in each group will receive treatment 3 times a week for 8 weeks. All treatments will be performed after skin cleansing, with patients wearing an eye mask and lying supine. All acupuncturists are licensed doctors with more than 3 years of experience in acupuncture treatment. Each treatment will last for 30 minutes. The temperature of the treatment room cannot be lower than 25°C.

Considering the participants' psychological state, they will be allowed to take regular oral administration of SSRIs. They must record the amount of SSRIs especially when they reduce the amount.

#### 2.5.1. Treatment Group

Participants in the treatment group will receive electroacupuncture treatment. Acupuncture method of each acupoint is shown in Table 2. Regular acupuncture method will be applied at Baihui (GV20), Shenting (GV24), Yintang (GV29), bilateral Anmian (EX-HN22), Shenmen (HT7), Sanyinjiao (SP6), and Neiguan (PC6). After needle insertion, rotating manipulation or lifting-thrusting manipulation will be applied for “Deqi” sensation. The electroacupuncture apparatus (CMNS6-1, Wuxi Jiajian Medical Device Co., Ltd., China) will be connected to the needles at Baihui (GV20) and Yintang (GV29) for 30 minutes and deliver a continuous wave to the patients. The frequency will be set at about 30 Hz and the amplitude will be less than 20 V during the treatment, based on the endurance of each patient.

#### 2.5.2. Control A Group

Participants in control A group will receive superficial acupuncture treatment at the following sham acupoints: bilateral acupoints 0.5 cun upper outer of Jiache (ST6), Waiguan (SJ5), Yangchi (SJ4), and Xuanzhong (GB39); acupoint upper outer of Quanliao (SI18); and bilateral acupoints in the middle of Tianyou (SJ16) and Tianrong (SI17). Acupuncturists will do no manipulation at each acupoint after inserting the needles. The electroacupuncture apparatus will be connected to the needles at bilateral acupoints 0.5 cun upper outer of ST6, with zero frequency and amplitude.

#### 2.5.3. Control B Group

Participants in control B group will receive sham acupuncture treatment at the same acupoints as control A group. The sham acupuncture will be applied with the placebo needles used in some trials before [22, 23]. When the tip of the blunt needles touches the skin, the patient will get a pricking sensation but there is no real needle inserted into the skin. The electroacupuncture apparatus will be set beside the patients, with no connection to the needles. Inform the patients when removing the needles after 30 minutes. Use the dry cotton ball to press the acupoints so that patients can feel the withdrawal of the “real” needles.

### 2.6. Outcome Measurement

#### 2.6.1. Primary Outcome

The Pittsburgh Sleep Quality Index (PSQI) is a widely used questionnaire to assess one's sleep disorders over one month. It is comprised of 19 self-rated items and 5 other-rated items [24]. The scores include the following indicators: subjective sleep quality, sleep latency, sleep duration, habitual sleep efficiency, sleep disturbances, use of medication, and daytime dysfunction. Each indicator is rated from 0 to 3. The accumulated scores of the seven indicators constitute the total score of PSQI (0–21). The higher score indicates the worse sleep quality and severer sleep disorders.

The Secondary outcomes are listed as follows:

